## 8.2 Analysis Endpoints

The study endpoints for evaluation are listed in [Section 3.2](#).

## 8.3 Analysis Sets

### 8.3.1 Safety Analysis Set

The Safety Analysis Set will include all randomized patients. Patients will be included in the group based on the fact that whether or not they actually consumed any amount of KB109: patients who actually consumed any amount of KB109 will be in the SSC + KB109 group; otherwise patients will be in the SSC alone group.

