#### **Statistical Methods:**

The study will enroll approximately 350 to 400 patients. The enrollment target is chosen for practical reasons. Assuming a 15% attrition rate, this will provide approximately 296 to 340 evaluable patients (148 to 170 per group). The precision of the point estimate in terms of half-width of the 95% confidence interval (CI) of the AE rate is summarized in [Table 4](#) for a range of evaluable number of patients and assumptions on the SP-related TEAE rates.

The analysis of AEs will be carried out on the Safety Analysis Set ([Section 8](#)). Summaries will be presented by Medical Dictionary for Regulatory Activities (MedDRA) system organ class and preferred term using frequency counts and percentages by group and overall.

The following endpoints will be analyzed based on the Full Analysis Set. The Kaplan-Meier method will be used to estimate median time to resolution of overall 13 COVID-19 related symptoms, overall 8 cardinal COVID-19 related symptoms, fever and resolution rate specific to each group. The change from Baseline to EOI in overall composite score of 13 COVID-19 related symptoms, overall composite score of 8 cardinal COVID-19-related symptoms, and bedrest time will be analyzed using analysis of covariance (ANCOVA) model. Proportion of patients with oxygen saturation <95% (or <98%) will be summarized by group using frequencies and percentages.

The following endpoints will be analyzed based on the Safety Analysis Set. Proportion of patients experiencing hospital admissions (all cause, and COVID-19-related) will be summarized by group using frequencies and percentages. Measures collected from the Healthcare Provider Wellness Visits and Healthcare Utilizations will be summarized by group using the following descriptive statistics: sample size, mean, standard deviation, median, minimum value, and maximum value or using frequencies and percentages.

More details of the statistical methods are provided in [Section 8](#). Methods related to exploratory objectives and supportive analyses will be described in a separate document such as Statistical Analysis Plan (SAP) which will be developed and completed prior to database lock.

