### 8.3.2 Full Analysis Set

The Full Analysis Set will include all randomized patients and have both Baseline and at least one post-Baseline endpoint observation during intake period. Patients will be analyzed in the group to which they were randomized.

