### 8.4.3 Analysis of Endpoints of Interest

#### Adverse Events (AEs)

The analysis of AEs will be based on the Safety Analysis Set. AEs will be coded using the most recent version of Medical Dictionary for Regulatory Activities (MedDRA).

A TEAE is defined as any AE starts or worsens in severity on or after the first dose of SP is taken for SSC + KB109 group or on or after the randomization for SSC group. Adverse event summary tables will include all TEAEs, SP-related TEAEs, SAEs, TEAEs by severity, and TEAEs leading to product discontinuation. Summaries will be presented by MedDRA system organ class and preferred term using frequency counts and percentages by group and overall.

The analysis of the following endpoints will be based on the Full Analysis Set unless otherwise specified.

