#### Time to resolution of fever

The Kaplan-Meier method will be used to estimate median time to resolution of fever and resolution rate specific to each group. Kaplan-Meier graphs will be generated; quartiles and point probabilities will be calculated. Interval estimates will be calculated using 95% point-wise CIs.

Proportion of patients with oxygen saturation <95% (or <98%) on Day 14 and Day 35, and proportion of patients experiencing hospital admissions during the Intake Period and Follow-up Period will be summarized by group using frequencies and percentages.

Measures collected from the Healthcare Provider Wellness Visits and Healthcare Utilizations during the Intake Period and Follow-up Period will be summarized by group based on the Safety Analysis Set using the following descriptive statistics: sample size, mean, standard deviation, median, minimum value, and maximum value or using frequencies and percentages.

Further details of the model specification, assumptions, and SAS implementation codes will be provided in the SAP.

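### The Safety Analysis Set counts KB109 patients who never take the product as SSC alone, and the Synopsis and Section 8.4.3 disagree on whether hospital admissions are tabulated in that set

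*Protocol*

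**What the plan says.** **Safety Analysis Set (Section 8.3.1).** Membership is complete: "The Safety Analysis Set will include all randomized patients". Grouping is by intake: a patient who took any KB109 goes to the SSC + KB109 group, and for everyone else the rule is "otherwise patients will be in the SSC alone group".

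**Full Analysis Set (Section 8.3.2).** It needs a Baseline value and at least one post-Baseline observation in the Intake Period. Grouping is by allocation: "Patients will be analyzed in the group to which they were randomized".

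**Hospital admissions.** The Synopsis (Statistical Methods) says: "The following endpoints will be analyzed based on the Safety Analysis Set. Proportion of patients experiencing hospital admissions". It puts wellness-visit measures and healthcare utilization in the same set. Section 8.4.3, after the adverse event paragraph, says: "The analysis of the following endpoints will be based on the Full Analysis Set unless otherwise specified". Under its fever heading it then states that the "proportion of patients experiencing hospital admissions during the Intake Period and Follow-up Period will be summarized by group using frequencies and percentages", and names no set. The next paragraph does name the Safety Analysis Set, for wellness measures and utilization.

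**TEAE start (Section 8.4.3).** A TEAE counts from the first dose in the SSC + KB109 group, but from randomization in the SSC group.

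**The concern.** A safety set grouped by product received normally leaves untreated patients out of the treated group. Here they are also added to the control group. In practice the transfer runs one way: Section 4.1 has KB109 shipped only where applicable, so SSC patients have none to take.

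The transfer may also be related to outcome. The kit is shipped after randomization, the Intake Period starts the morning after it arrives (Section 4.1), and hospitalization for worsening COVID-19 ends participation (Section 5.5). A patient who deteriorates before taking any product can therefore become a permanent never-taker, whose events are then shown under SSC.

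At stake are the by-group percentages for a hard clinical outcome and for the all-TEAE and SAE tables, which serve a primary objective worded as a comparison of the two arms. Separately, the plan gives two instructions for one secondary endpoint, and both cannot be followed.

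**Working it through.** **1. Passages side by side**

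| Endpoint | Synopsis | Section 8.4.3 | A KB109 never-taker is counted in |
|---|---|---|---|
| Hospital admissions | Safety Analysis Set | Full Analysis Set by default | SSC (Synopsis) or KB109 (8.4.3, if in the set) |
| Wellness measures, utilization | Safety Analysis Set | Safety Analysis Set | SSC |
| Adverse events | Safety Analysis Set | Safety Analysis Set | SSC |

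Hospital stay is itself one of the utilization items (Section 4.3.7). Even within Section 8.4.3 the same event can therefore be grouped as randomized in one table and by consumption in another.

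**2. Inputs**

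- From the protocol: 1:1 allocation, 175 to 200 patients per group.
- Not in the protocol, so assumed: 2% to 5% admitted; the number of KB109 never-takers; how many of those are admitted.
- No stated figure bears directly on this point. The per-group evaluable numbers in Section 8.1 do reproduce (175 × 0.85 = 148.75, given as 148; 200 × 0.85 = 170).

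**3. Formula**

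Take two arms of n patients with e admissions each, so there is no true difference. Move m never-takers, of whom k are admitted, from KB109 to SSC:

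difference = (e − k)/(n − m) − (e + k)/(n + m) = −2n(k − m·e/n)/(n² − m²)

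The shift depends on the excess k − m·e/n, that is, admissions among never-takers beyond what the arm average would give. Each excess admission moves the difference by about 2/n, which is 1.0 point at n = 200 and 1.1 points at n = 175.

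**4. Results, starting from equal randomized arms**

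| n | e | m | k | KB109 as tabulated | SSC as tabulated | Difference (points) |
|---|---|---|---|---|---|---|
| 175 | 4 | 1 | 1 | 3/174 = 1.72% | 5/176 = 2.84% | −1.12 |
| 175 | 9 | 1 | 1 | 8/174 = 4.60% | 10/176 = 5.68% | −1.08 |
| 200 | 4 | 1 | 1 | 3/199 = 1.51% | 5/201 = 2.49% | −0.98 |
| 200 | 10 | 1 | 1 | 9/199 = 4.52% | 11/201 = 5.47% | −0.95 |
| 200 | 10 | 6 | 2 | 8/194 = 4.12% | 12/206 = 5.83% | −1.70 |
| 200 | 10 | 10 | 3 | 7/190 = 3.68% | 13/210 = 6.19% | −2.51 |
| 200 | 10 | 10 | 0.5 (arm average) | 9.5/190 = 5.00% | 10.5/210 = 5.00% | 0 |
| 200 | 10 | 10 | 0 | 10/190 = 5.26% | 10/210 = 4.76% | +0.50 |

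The sixth row assumes that 30% of never-takers are admitted, six times the arm average. In the last row, where no never-taker is admitted, the sign reverses.

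**5. Primary endpoint**

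Section 7.3 judges relatedness by possible causation by the product and its timing relative to administration. A never-taker should have essentially no SP-related event. With an assumed 20% rate and 10 never-takers, 40/200 = 20.0% becomes 40/190 = 21.1%. The SSC numerator does not change.

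**6. TEAE start**

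Combine Section 8.3.1 with the TEAE definition. An event between randomization and first dose in a KB109 patient is not a TEAE if the patient later doses. If the patient never doses, the same event becomes an SSC TEAE. Section 7.3.3 excepts hospitalizations from the rule that disease symptoms are not TEAEs, so serious events can enter this way.

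**The case against.** - **Grouping by product received is common for adverse events, and the plan is descriptive.** True, and no test or decision rule depends on these tables. But the common practice does not require adding unexposed patients of one arm to the other, and the by-group percentages are the comparison that will be read.
- **A reader might infer that the primary endpoint is tilted toward KB109.** The documents do not support this. The endpoint is SP-related TEAEs, and step 5 shows a small effect in the opposite direction.
- **A reader might infer that early failures on KB109 in general are charged to SSC.** They are not. Anyone who took any amount stays in the KB109 group, however soon they fail.
- **A reader might infer that admissions while the kit is in transit drive the bias.** Section 3.2.2 counts admissions in the Intake and Follow-up Periods only, so those before Day 1 are outside the endpoint. What remains is patients who reach Day 1, never dose and are then admitted. With overnight shipping and dosing due on Day 1, that group may be small. The TEAE table has no such limit.
- **Section 8.4.3 already groups admissions as randomized.** It does so by default, so the contradiction can be removed by editing. The Full Analysis Set is still not ideal, because a patient admitted before any post-Baseline observation drops out of it, although this applies to both arms.
- **The size is assumed.** This stands: the protocol gives no admission rate and no non-starter rate, and it excludes patients judged likely to need hospitalization.

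**Conclusion.** The point holds in limited form. The contradiction over the analysis set for hospital admissions is plain on the text, whatever the size of any bias. The transfer of KB109 never-takers to SSC is also plain, and it can distort admissions from Day 1 on, utilization, all-cause TEAEs and SAEs. The distortion favors KB109 only if never-takers have more events than average. On the assumed inputs it is about 1 percentage point per admitted never-taker at 175 to 200 per arm, against assumed admission rates of 2% to 5%. It is zero at the arm average and reverses below it. The different TEAE start dates add to the problem. The primary endpoint is affected only through a slightly smaller KB109 denominator. Severity: should-fix.

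**What to change.** 1. **Admissions, utilization, wellness measures.** Analyse them in all randomized patients by randomized arm, and say so in the same words in the Synopsis and Section 8.4.3.
2. **Adverse events.** Remove from Section 8.3.1 the rule that places KB109 never-takers in SSC alone. Then either show them as a separate, listed category, or compare all-cause TEAEs and SAEs by randomized arm with one common start (randomization or Day 1) for both arms. Regrouping by randomized arm without a common start is not enough: under the present definition a KB109 never-taker has no first dose and so no countable TEAE.

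**Cost.** Wording in the Synopsis and Sections 8.3.1 and 8.4.3; no new data. The by-arm table will include a few unexposed KB109 patients. The separate category takes patients out of one arm after randomization, so it should be read as descriptive.

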### 8.3.2 Full Analysis Set

The Full Analysis Set will include all randomized patients and have both Baseline and at least one post-Baseline endpoint observation during intake period. Patients will be analyzed in the group to which they were randomized.

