### **Part 2, Intake Period**

The Intake Period (Days 1-14) will begin the morning after receipt of the KaSK. All patients will continue to follow the SSC guidance as provided by the treating healthcare provider throughout study participation. In the Intake Period, all patients will continue to record their daily COVID-19-related symptoms, selected COVID-19 signs, responses to questions related to QOL measures, healthcare utilization measures, and concomitant medications taken in the previous 24 hours using TrialPace™ where appropriate. Patients randomized to SSC + KB109 will begin consuming KB109 on Day 1 after recording the required information. All KB109 usage will be noted in the patient's SP log. For all patients in both groups, temperature and oxygen saturation will be measured and recorded as needed throughout the day prior to taking anti-pyretic medication.

Wellness visits by telephone call between Day 1 and Day 14 will be conducted to follow-up on the patient's health status, to ascertain compliance with SP usage or completion of TrialPace™ questions, and to reeducate the patient on the importance of adherence to study instructions including SP usage (where applicable). When wellness and telemedicine visits fall on the same day, they will be combined as a telemedicine visit.

On Day 14, all patients will undergo a telemedicine visit where the following will be conducted: an abbreviated physical examination, an assessment of safety and other protocol-specified measures of health, and an evaluation of whether follow-up treatment is recommended due to a deterioration of COVID-19 symptoms. Patients in the SSC + KB109 group will stop taking KB109 on Day 14. If feasible blood samples for clinical chemistries, biomarkers and serological measures of immunity, and nasal/oropharyngeal swabs for quantitative viral load assessments (research purposes only), will be collected; sample collection may occur at the patient's home by a healthcare professional, remotely, or at the study site or clinic.

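### The Full Analysis Set demands a Baseline and an Intake-Period observation that several of its endpoints do not use, and the protocol assigns hospital admissions to two different analysis sets

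*Protocol*

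**What the plan says.** Section 8.3.2: "The Full Analysis Set will include all randomized patients and have both Baseline and at least one post-Baseline endpoint observation during intake period". Patients in this set are analyzed in the group to which they were randomized.

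Section 8.3.1: "The Safety Analysis Set will include all randomized patients". It has no data requirement, but it groups patients by whether they actually consumed any KB109, so a patient who took none is placed under SSC alone whatever the allocation.

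Section 8.4.3, after the adverse-event paragraph: "The analysis of the following endpoints will be based on the Full Analysis Set unless otherwise specified". Time to resolution (13 symptoms, 8 symptoms, fever), the composite change scores and oxygen saturation follow on that basis, and the Synopsis agrees.

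On hospital admissions the two places differ:
- Synopsis, Statistical Methods: "The following endpoints will be analyzed based on the Safety Analysis Set", and the first endpoint listed is "Proportion of patients experiencing hospital admissions (all cause, and COVID-19-related) will be summarized by group using frequencies and percentages".
- Section 8.4.3, under time to resolution of fever: "proportion of patients experiencing hospital admissions during the Intake Period and Follow-up Period will be summarized by group using frequencies and percentages", with no set named. The next paragraph does name the Safety Analysis Set, for wellness-visit measures and healthcare utilization.

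On timing, Section 4.1 has the kit shipped overnight once the patient is randomized, and "The Intake Period (Days 1-14) will begin the morning after receipt of the KaSK".

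**The concern.** A set meant to preserve the randomized comparison should not depend on data that arise after patients know their arm. Here membership does, and the data requirement goes beyond what several endpoints need. If patients who learn they are on SSC alone stop recording more often than those given product, exclusions could differ between groups.

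Admissions are the endpoint where the choice of set could matter most. A patient who is admitted early may supply no further data, and Section 5.5 discontinues patients hospitalized for worsening COVID-19. The protocol leaves open which of two sets applies, and each handles such a patient awkwardly.

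**Working it through.** **The plan's own figures.** Section 8.1: 350 × 0.85 = 297.5, or 148.75 per group, rounded down to 148, and 2 × 148 = 296; 400 × 0.85 = 340, or 170 per group. All eight rows of Table 4 reproduce with exact Clopper-Pearson intervals (for example 15/148 gives 5.8% to 16.2%, half-width 5.2%). None of these figures depends on the Full Analysis Set definition, so nothing stated there changes.

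**Step 1: which endpoints need what.**

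| Endpoint | Set | Needs a Baseline value? | Needs an Intake-Period value? |
|---|---|---|---|
| Composite change to end of intake | Full | Yes | Yes |
| Individual symptom reduced or absent | Full | Yes, symptom present at Baseline | Only for the end-of-intake version |
| Time to resolution, symptoms and fever | Full | No, runs from Day 1 on the score or temperature itself | In practice yes |
| Saturation below 95% or 98% | Full | No | Day 14 yes, Day 35 no |
| Hospital admission | Safety (Synopsis) or Full by default (8.4.3) | No | No |

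Two groups with usable data are dropped: patients with Intake-Period records but no Baseline (time to resolution, saturation), and patients whose only saturation is at Day 35.

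**Step 2: how often a Baseline could be missing.** For symptoms, rarely. Section 4.3.4 starts the diary after consent, and Section 8.4.3 accepts any non-missing value on Day -2, -1 or 1. For temperature and saturation the position is weaker. The thermometer and oximeter come in the kit shipped after randomization (Section 4.1 and footnote 5 of Table 1), so a Baseline from the study devices is itself recorded after allocation.

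**Step 3: admissions under each set.**
- *Full Analysis Set.* A patient admitted before any post-Baseline observation can leave both numerator and denominator. With admission rate p and a fraction f of admitted patients lacking that observation, and no other exclusions, the set would show p(1 − f)/(1 − pf). The protocol gives neither p nor f, so the values below are assumptions:

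| Assumed p | f = 10% | f = 25% | f = 50% |
|---|---|---|---|
| 2% | 1.8% | 1.5% | 1.0% |
| 5% | 4.5% | 3.8% | 2.6% |
| 10% | 9.1% | 7.7% | 5.3% |

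For example, 0.05 × 0.75 / (1 − 0.0125) = 3.8%. Admissions lost are n × p × f: from 175 × 0.02 × 0.10 = 0.4 to 175 × 0.10 × 0.50 = 8.8 per group of 175, and from 0.4 to 10 per group of 200.
- *Safety Analysis Set.* The patient is kept, but one randomized to SSC + KB109 and admitted with no dose taken counts under SSC alone. Assume 200 per group and 10 admissions in each (5%). One such in-window admission turns 10/200 against 10/200 into 9/199 = 4.5% against 11/201 = 5.5%, a difference of about 1 percentage point created by grouping alone.
- *Either set.* The endpoint covers the Intake and Follow-up Periods only. Overnight shipping and then the next morning put Day 1 about two days after randomization if the kit leaves the same day. Admissions in that gap are outside the window, although Section 7.4.3 collects serious adverse events from consent.

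**The case against.** The strongest reply is that the Synopsis places admissions on the Safety Analysis Set, that the default in Section 8.4.3 gives way where something else is specified, and that the Synopsis specifies it. On that reading no early admission is lost through the Full Analysis Set. This is a reasonable reading and may be what was intended. But Section 8.4.3 names the Safety Analysis Set for the very next group of endpoints and not for admissions, so a programmer working from Section 8 would use the Full Analysis Set. The contradiction stands, and the Safety Analysis Set still does not keep patients as randomized.

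Other parts of the reply also have force:
- The criterion is an endpoint observation, not a diary entry. Wellness calls on Days 3, 7 and 10, or an Intake-Period admission itself, might qualify. Under the Full Analysis Set, early admissions can therefore be lost but need not be.
- Inpatient hospitalizations are reported as serious adverse events and tabulated on the Safety Analysis Set, so early ones are not hidden from the study report.
- A time-to-resolution patient with no post-Baseline record would be censored at about Day 1 and add almost nothing.
- The analyses are descriptive, and Section 8.4.1 reports the size of each set by group, so unequal exclusion would be visible.

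These points limit the consequence. They do not supply a reason for requiring a Baseline where the endpoint does not use one.

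**Conclusion.** The point holds in a limited form. The Full Analysis Set excludes randomized patients on a condition broader than time to resolution and oxygen saturation require, and part of that condition is met only after an open-label allocation. The number affected is probably small, and the protocol gives no basis for estimating it. The admissions endpoint has two conflicting analysis sets. Neither gives all randomized patients as randomized, and its window leaves out the interval from randomization to Day 1.

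The admission figures above show how the arithmetic works under assumed rates; they are not estimates for this trial. A reader might infer more than the documents support in four ways:
- That early admissions certainly vanish: they can do so only under the Section 8.4.3 default, which the Synopsis contradicts.
- That patients lost before a first diary entry are the issue: symptom diaries begin after consent, so what matters is the first post-Baseline observation in the Intake Period.
- That exclusions will differ by arm by a known amount: no passage gives one.
- That the main results are compromised: the primary endpoint uses all randomized patients, and the change-from-Baseline models need both values anyway.

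**What to change.** 1. In Section 8.3.2, define the Full Analysis Set as all randomized patients, analyzed as randomized.
2. In Section 8.4.3, require a Baseline value only for the change-from-Baseline models. The symptom-reduction and symptom-absence proportions already call for one by their own definition.
3. Reconcile the Synopsis with Section 8.4.3 on admissions: summarize them in all randomized patients, as randomized, from randomization to Day 35 or last contact. Take admissions before Day 1 and after discontinuation from the serious adverse event reports, as far as these reach. State the same window in Section 3.2.2.
4. Say how patients with no post-randomization record are handled: censored at the start for time to resolution, and reported as missing for saturation.

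The cost is a few sentences and no new data collection. The drawback is that a few patients with little or no data are carried in the denominators, so the number with missing values should be shown by group.
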